#### Sample size calculation

Based on the preliminary results of clinical research, no less than an estimated 55% total efficiency will be obtained with JWQTP treatment and approximately 30% will be obtained with the intervention of a placebo. Using a superiority test, no fewer than 66 subjects should be enrolled based on α = 0.05, β = 0.15 and power = 0.85 in each treatment group. Allowing for a 20% drop-out, we therefore propose the recruitment of a total sample size of 240 patients, with average distributions among the three groups.

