### Outcome measurement

#### Primary outcome

The eradication of epigastric pain is considered the primary outcome to evaluate therapeutic effects. The visual analogue scale (VAS) score (0 to 10 numeric pain intensity scale) for epigastric pain was measured at every visit, ranging from 0 to 10, where a score of 0 suggests no epigastric pain and a score of 10 indicates the most severe epigastric pain. The eradication of epigastric pain is defined as a score of VAS that stops rising after dropping to 0 during the study. The eradication rate of epigastric pain will be compared among the three groups, together with the change in VAS scores before and after treatment in each group.

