The classification of treatment efficacy is shown as follows: CMTEI ≥95% indicates clinical recovery; 95% > CMTEI ≥70% indicates remarkable recovery; 70% > CMTEI ≥30% indicates modest recovery; and CMTEI < 30% indicates inefficiency.

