An analysis of variance (ANOVA) or chi-square test will be used to compare baselines among patients, including demographic data, vital signs, history of diseases, basic treatment and so on. For the comparison of variations from the baseline to endpoint, Student’s t-test will be performed on variables with normal distributions, and the Wilcoxon rank sum test will be performed on variables with non-normal distributions. The evaluation of therapeutic effects will primarily be performed between baseline and visit six, in compliance with PPS, or the time to withdraw from the study, in compliance with FAS. In addition, the changes from baseline to visits two, three, four or five will be evaluated. For continuous variables regarding therapeutic effect, an ANOVA will be used for multiple comparisons of variation from baseline among different groups, and Dunnett’s tests will be used for comparisons within a group. A covariance analysis, adjusted for the baseline covariate, will be used to evaluate the differences of the symptom scores, VAS scores and PRO instrument scores among the groups considering the center effect. The least square mean in each group and the 95% confidence intervals of mean differences among groups will be calculated. The Cochran-Mantel-Haenszel test, stratified by center effect, and the logistic regression model, adjusted for covariates, will be used on categorical variables in addition to the chi-square test, Wilcoxon rank sum test or Fisher’s exact test. The total drop-out rate in each group will be compared with the drop-out rate due to AEs for drop-out analyses using chi-square test or Fisher’s exact test. For safety analyses, we will perform the chi-square test or Fisher’s exact test to evaluate the incidence rate of AEs among the groups and describe AEs using descriptive statistics through listing.

All statistical tests will be performed by an independent statistician using SAS 9.2, assuming a two-sided test and a 0.05 level of significance.

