## Discussion

To date, CNG remains unclear and has no specific remedy. The presence or absence and severity of dyspepsia have no obvious correlations with the histopathological findings and endoscopic grading of CG [3]. The therapeutic aim of CNG is to ameliorate these symptoms and to reduce the inflammation of the gastric mucosa, mainly focusing on the eradication of HP, prokinetics, antacids (H2-receptor antagonist or a proton pump inhibitor), mucosal-protective agents, anti-depression drugs and anti-anxiety drugs [5]. However, many CNG patients suffer from recurrent bouts of dyspeptic symptoms because these symptoms are easily influenced by psychological, social or dietary factors. TCM was more effective than chemotherapy in the treatment of chronic gastritis, including all subtypes, and no serious side effects have been identified. TCM has been widely considered an alternative option for chronic gastritis in East Asia [7,21]. According to the present findings, no scientifically rigorous trials have been designed to treat CNG patients with SSQDDSS. This study will be the first to explore the efficacy and safety of JWQTP and to provide evidence and an optimal dosage for a phase III clinical trial.

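### The 85% power is stated for an undefined total efficiency rate (55% vs 30%) that nothing ties to the primary outcome, eradication of epigastric pain

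*Protocol article*

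**What the plan says.** All references are to the protocol article.

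- **Primary outcome:** "The eradication of epigastric pain is considered the primary outcome to evaluate therapeutic effects". It is reached when the VAS score falls to 0 and does not rise afterwards. The Abstract names the same outcome.
- **Sample size calculation, rates:** "no less than an estimated 55% total efficiency will be obtained with JWQTP treatment". The placebo figure is about 30%. Both are attributed to preliminary clinical research.
- **Sample size calculation, size:** "no fewer than 66 subjects should be enrolled based on α = 0.05, β = 0.15 and power = 0.85 in each treatment group". Then: "Allowing for a 20% drop-out, we therefore propose the recruitment of a total sample size of 240 patients".
- **Statistical analysis:** tests are run "assuming a two-sided test and a 0.05 level of significance". The full analysis set is primary, with last observation carried forward (LOCF) so that the analysed population matches the one that entered.
- **The treatment efficacy in the Chinese medicine field (a secondary outcome):** the therapeutic effect index (CMTEI) is the percentage fall in a symptom score. It has four grades, the lowest being "CMTEI < 30% indicates inefficiency".

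**The concern.** The paragraph that sets the power uses a term found nowhere else in the article. It does not mention pain, VAS or eradication. The only outcome graded in similar words is the CMTEI, so the natural reading of total efficiency is the share of patients with a CMTEI of at least 30%. That is a secondary outcome and a different event from losing all epigastric pain.

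If the 55% and 30% belong to another endpoint, the 85% power belongs to it too. The trial is meant to inform a phase III programme and a choice of dose. A non-significant primary result would then be read against a power that was never worked out for that test, and an inconclusive result could be taken for an inactive drug.

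**Working it through.** **1. Reproducing the stated size.** Inputs from the article: p1 = 0.55, p2 = 0.30, two-sided α = 0.05 (z = 1.960), power 0.85 (z = 1.036). The article gives no formula. The unpooled normal approximation for two proportions reproduces its figure:

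n = (1.960 + 1.036)² × (0.55×0.45 + 0.30×0.70) / 0.25² = 65.7, so 66 per arm.

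The pooled-variance version gives 69 per arm, and 83.6% power at 66. For drop-out, 66 × 1.2 = 79.2, so 80 per arm and 240 in total. The calculation is correct for 55% vs 30%.

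**2. Are the two endpoints the same event?** Table 3 lets us check total efficiency read as a CMTEI of at least 30%. The primary symptom scores up to 6 + 6 = 12, and the secondary symptoms up to 2 + 2 + 3 + 3 + 2 + 2 = 14.

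- *Improved on the index with pain still present:* a patient starts at 12 + 14 = 26. Pain falls to degree 2 and duration 2, and the secondary symptoms do not change, giving 18. The CMTEI is 8/26 = 31%, above the lowest grade, without eradication.
- *Pain eradicated but graded lowest:* a patient starts at 4 + 14 = 18, loses all pain and keeps the secondary symptoms, giving 14. The CMTEI is 4/18 = 22%.

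Neither event contains the other, so a rate for one cannot be carried over to the other.

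**3. Power of the primary test under assumed eradication rates.** The article gives no eradication rate, so every row except the first is an assumption. The comparison is one dose group against placebo, with the formula that reproduces 66:

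power = Φ( (p1 − p2) × √(n / V) − 1.960 ), with V = p1(1 − p1) + p2(1 − p2).

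Example, 40% vs 20% at n = 66: V = 0.24 + 0.16 = 0.40, and 0.20 × √(66/0.40) − 1.960 = 0.609, so power is 72.9%.

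| JWQTP vs placebo | V | Power, 66 per arm | Power, 80 per arm |
|---|---|---|---|
| 55% vs 30% (article's total efficiency) | 0.4575 | 85.1% | 91.1% |
| 40% vs 20% | 0.4000 | 72.9% | 80.7% |
| 25% vs 10% | 0.2775 | 63.8% | 72.1% |
| 30% vs 15% | 0.3375 | 55.5% | 63.7% |
| 35% vs 20% | 0.3875 | 49.9% | 57.7% |
| 30% vs 10% | 0.3000 | 84.3% | 90.4% |
| 35% vs 10% | 0.3175 | 95.0% | 97.8% |

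The 80-per-arm column matches the primary analysis, because the full analysis set with LOCF keeps everyone who entered.

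**The case against.** **Total efficiency may be a loose rendering of the eradication rate.** The term is undefined, and the CMTEI section speaks only of inefficiency, for one grade out of four. This stands. The link to the CMTEI is a strong inference and not a fact in the text. Even so, the reader cannot tell which endpoint was powered, so the paragraph needs correcting on either reading.

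**A reader might infer that the trial is underpowered.** The article does not support that. It gives no eradication rate, and some plausible pairs keep the power high.

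**A reader might infer that the full 25-point difference must carry over to pain eradication.** It need not. Lower rates mean a smaller variance, so a smaller gap can be enough. At 66 per arm, 25% vs 5% gives V = 0.2350 and 92% power, and 32% vs 10% gives V = 0.3076 and 90%.

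**66 per arm is not what the primary analysis has.** This stands. With 80 per arm, power in the four weakest rows rises by about 8 points, though all four stay below 85%. LOCF may itself change the observed rates, which the table does not capture.

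**A reader might set the cited preliminary results against the Discussion's "This study will be the first to explore the efficacy and safety of JWQTP".** That is no contradiction. The Abstract limits the claim of being first to a multicentre, double-blind, randomised, placebo-controlled trial, and earlier, less rigorous clinical work can exist beside it.

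**A condensed article may leave the source of its rates to the full protocol.** That is fair for the source. It does not cover the endpoint: the article presents a whole calculation and names in it something other than its primary outcome.

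**Conclusion.** The point holds as one of an undefined and unlinked endpoint. The 66 per arm is right for 55% vs 30%, but nothing shows that these are pain-eradication rates, so the 85% power is not established for the primary test. Whether the true power is higher or lower cannot be decided from the article. Over the assumed pairs in the table it lies between about 50% and 95% with 66 per arm, and between about 58% and 98% with 80. These figures rest on the assumed rates, on the unpooled two-sided formula inferred from the stated 66, and on a single dose-versus-placebo comparison at 0.05.

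**What to change.** Keep 240 patients and rewrite the sample size paragraph:

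1. Name eradication of epigastric pain as the endpoint of the calculation, and state the assumed eradication rates for JWQTP and placebo from the preliminary data.
2. Report the power that 80 per arm gives for those rates, with a short table over plausible rates, and state the formula.
3. If total efficiency was meant to be the eradication rate, say so and use one term throughout. If it was the CMTEI response, define it and present its power as that of a secondary outcome.

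The cost is one paragraph and no extra patients. The article reports that recruitment had not yet begun, so the change could precede any data. The downside is that the stated power may become less favourable.

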### Randomization

For randomization, the participants will be assigned into a high-dose group, a low-dose group or a placebo control group, with a 1:1:1 ratio using a stratified randomization method, with stratification by center. The randomization sequence will be created at the West China Hospital of Sichuan using SAS 9.2 software to determine the appropriate segment. Two copies of the randomization list will be kept in safe places - one by the West China Hospital of Sichuan University drug clinical trial agency and one by the sponsor of this study - during the study period. Each patient will receive a unique randomized test number corresponding to the specified drug, according to the group allocation. An emergency envelope has been prepared for each test number and is to be opened for treatment allocation only due to medical emergency.

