#### Statistical analysis

A full analysis set (FAS) is the primary analysis population for efficacy with an intention-to-treat principle. We estimate the missing data using the last observation carried forward (LOCF) method so that the population for the final analysis corresponds with that at the beginning of this study. The per-protocol set (PPS), in which all subjects enable themselves to finish the study according to the protocol, represents a subcardinal analysis population for efficacy. Descriptive statistics will be presented as the means, standard deviations, medians, minimum values and maximum values for continuous variables and as frequencies and percentages for categorical variables.

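### The sample-size figures do not fit together: 240 patients less 20% drop-out leaves 64 completers per arm, not the required 66, with only a small effect on power

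*Protocol article*

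**What the plan says.** The Sample size calculation section of the protocol article assumes that "no less than an estimated 55% total efficiency will be obtained with JWQTP treatment" and that "approximately 30% will be obtained with the intervention of a placebo". From these rates it concludes that "no fewer than 66 subjects should be enrolled", "based on α = 0.05, β = 0.15 and power = 0.85 in each treatment group". It then moves from 66 per group to the total: "Allowing for a 20% drop-out, we therefore propose the recruitment of a total sample size of 240 patients", divided equally among the three groups. Equal division agrees with the Randomization section, which allocates "with a 1:1:1 ratio using a stratified randomization method", so each arm has 80 patients.

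Two statements in the Statistical analysis section bear on the point. Tests are run "assuming a two-sided test and a 0.05 level of significance". The analysis population is fixed as follows: "A full analysis set (FAS) is the primary analysis population for efficacy with an intention-to-treat principle". Missing values are filled by last observation carried forward (LOCF) so that the number analysed matches the number who started. The per-protocol set is the secondary efficacy population.

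**The concern.** The section gives four figures that should be linked by simple arithmetic: at least 66 per group, power 0.85, a 20% drop-out allowance and 240 patients in total. If the 66 are the patients who must remain after drop-out, which is the usual purpose of such an allowance, 80 per arm is slightly too few.

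What is at stake is mainly the accuracy of the published sample-size justification. A reader will take it that the trial tolerates 20% drop-out and still has the patients needed for 85% power. By the article's own figures it tolerates 17.5%. The section also does not say which analysis population the 66 refers to, so the reader cannot tell which analysis the allowance is meant to protect.

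**Working it through.** **Inputs.** From Sample size calculation: rates 0.55 and 0.30, alpha 0.05, power 0.85, 66 per group, 20% drop-out, 240 in total. From Statistical analysis: two-sided tests. From Randomization: 1:1:1 allocation. All power figures below are for one dose group against placebo at two-sided 0.05, as the article calculates it.

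**Step 1: reproduce 66.** Unpooled normal approximation for two proportions:

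n = [p1(1 − p1) + p2(1 − p2)] × (z for two-sided 0.05 + z for power 0.85)² / (p1 − p2)²

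- Variance term: 0.55 × 0.45 + 0.30 × 0.70 = 0.2475 + 0.2100 = 0.4575
- n = 0.4575 × (1.960 + 1.036)² / 0.25² = 65.7, rounded up to 66

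The stated 66 is reproduced exactly, so this formula is used below.

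**Step 2: the drop-out allowance.**

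- Enrolled per arm: 240 / 3 = 80
- Left after 20% loss: 80 × 0.8 = 64, which is 2 below 66
- Needed to keep 66 after 20% loss: 66 / 0.8 = 82.5, so 83 per arm and 3 × 83 = 249 in total
- Gap: 3 per arm, 9 in total
- Drop-out that 80 per arm does cover: 1 − 66/80 = 17.5%
- Likely origin of 240: 66 × 1.2 = 79.2, rounded up to 80, and 3 × 80 = 240. This is inferred from the figures.

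**Step 3: power at the relevant sizes.** Power = Φ(0.25 / √(0.4575/n) − 1.960):

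| n per arm | Meaning | Power |
|---|---|---|
| 66 | stated minimum | 0.851 |
| 64 | completers after 20% loss from 80 | 0.841 |
| 80 | all randomised, as in the full analysis set | 0.911 |

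At 80 per arm the pooled-variance version gives 0.90, so 0.90 to 0.91 is a fair range for the full analysis set.

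**Step 4: does the figure at 80 hold when drop-outs are carried forward?** It requires drop-outs to reach pain eradication at the same 55% and 30% as completers, which the article does not state. As an illustration (my assumption), let 20% drop out of each arm and let their success rate be a fraction f of the completers' rate. The arm rates become 0.55 × (0.8 + 0.2f) and 0.30 × (0.8 + 0.2f). With 80 analysed per arm and the same unpooled formula:

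| f | Arm rates | Power |
|---|---|---|
| 1 | 0.550 v 0.300 | 0.91 |
| 0.5 | 0.495 v 0.270 | 0.85 |
| 0.25 | 0.4675 v 0.255 | 0.82 |
| 0 | 0.440 v 0.240 | 0.78 |

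**The case against.** The strongest reply is that the primary analysis does not lose drop-outs at all. The Statistical analysis section makes the full analysis set primary and fills missing values by LOCF, so about 80 per arm enter the primary comparison, with power above the stated 85% at the assumed rates. The figure of 64 belongs to a completer or per-protocol analysis, which is secondary. Even there the loss is about one percentage point. This stands, and it rules out reading the slip as a failure of the trial's primary power. It does not make the stated figures consistent: the section inflates for drop-out as if those patients were lost. Nor does it guarantee 85%, because the power in the full analysis set depends on how carried-forward drop-outs respond.

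A second reply is that 240 may be a practical choice. The Patient population and setting section plans 48 patients at each of five sites, which is 16 per arm per site, and 249 does not divide by five. That is possible, and because no inflation formula is given, multiplication by 1.2 remains an inference. The shortfall of 64 against 66 does not depend on it.

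A reader might also infer that 66 is itself too low, because a pooled-variance formula gives 69 per arm and Fisher's exact test has power of only 0.78 at 64 per arm. The article does not support this as an error. Its 66 follows exactly from a standard formula, and Fisher's test is one of several listed for categorical variables, not named as the primary test. Those differences come mainly from the choice of approximation or test, not from the drop-out step.

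**Conclusion.** The inconsistency is real and minor. With 240 patients and 20% drop-out, 64 complete per arm against the stated minimum of 66; 249 patients would be needed to keep 66. In a completer or per-protocol analysis the cost is about one point of power, 0.84 instead of 0.85, taking 20% as the whole loss from that set and the 55% and 30% rates as given.

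The tempting stronger conclusion, that the trial misses its stated 85% power, is not supported. The primary analysis keeps about 80 per arm and has power of about 0.90 to 0.91 if drop-outs respond at the assumed rates. In the illustration it falls to about 0.85 if they respond at half the completers' rate and to about 0.78 if all are failures. The article does not say which of these to expect, so it establishes neither a shortfall nor a margin in the primary analysis.

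**What to change.** Keep 240 patients and correct the sentence so that it states the drop-out the number covers and names the population. For example:

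> Eighty patients per arm allow for 17.5% drop-out while leaving 66 completers. At 20% drop-out, 64 completers per arm give about 84% power in the per-protocol analysis. The primary analysis, in the full analysis set, retains all randomised patients by LOCF.

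If the sponsor also wishes to quote power for the full analysis set, it should state the response rate assumed for drop-outs.

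The cost is a few lines of text and a slightly less favourable drop-out figure. Recruitment, the site plan, the randomisation and the primary analysis are unchanged.

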#### Statistical analysis

A full analysis set (FAS) is the primary analysis population for efficacy with an intention-to-treat principle. We estimate the missing data using the last observation carried forward (LOCF) method so that the population for the final analysis corresponds with that at the beginning of this study. The per-protocol set (PPS), in which all subjects enable themselves to finish the study according to the protocol, represents a subcardinal analysis population for efficacy. Descriptive statistics will be presented as the means, standard deviations, medians, minimum values and maximum values for continuous variables and as frequencies and percentages for categorical variables.

An analysis of variance (ANOVA) or chi-square test will be used to compare baselines among patients, including demographic data, vital signs, history of diseases, basic treatment and so on. For the comparison of variations from the baseline to endpoint, Student’s t-test will be performed on variables with normal distributions, and the Wilcoxon rank sum test will be performed on variables with non-normal distributions. The evaluation of therapeutic effects will primarily be performed between baseline and visit six, in compliance with PPS, or the time to withdraw from the study, in compliance with FAS. In addition, the changes from baseline to visits two, three, four or five will be evaluated. For continuous variables regarding therapeutic effect, an ANOVA will be used for multiple comparisons of variation from baseline among different groups, and Dunnett’s tests will be used for comparisons within a group. A covariance analysis, adjusted for the baseline covariate, will be used to evaluate the differences of the symptom scores, VAS scores and PRO instrument scores among the groups considering the center effect. The least square mean in each group and the 95% confidence intervals of mean differences among groups will be calculated. The Cochran-Mantel-Haenszel test, stratified by center effect, and the logistic regression model, adjusted for covariates, will be used on categorical variables in addition to the chi-square test, Wilcoxon rank sum test or Fisher’s exact test. The total drop-out rate in each group will be compared with the drop-out rate due to AEs for drop-out analyses using chi-square test or Fisher’s exact test. For safety analyses, we will perform the chi-square test or Fisher’s exact test to evaluate the incidence rate of AEs among the groups and describe AEs using descriptive statistics through listing.

All statistical tests will be performed by an independent statistician using SAS 9.2, assuming a two-sided test and a 0.05 level of significance.

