	+++ (severe): A dense accumulation of chronic inflammatory cells occupying the whole depth of the mucosa	3
**Active chronic inflammation**	Normal	0
	+ (mile): Few neutrophils in the lamina propria of the mucosa	1
	++ (moderate): More neutrophils in the mucosal layer and between superficial epithelial cells, pit epithelial cells and glandular epithelial cells.	2
	+++ (severe): A more dense infiltration of neutrophils, or abscess on pits can be seen in addition to what is seen in moderate activity.	3

^**a**^Two to five biopsy specimens reaching musculature in the mucosa will be taken from gastric antral, gastric angle or suspected focal lesions of sufficient size. For the specimens taken at the first and sixth visits, the regions should be chosen consistently as possible as it can.

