#### Secondary outcomes

##### Endoscopic and histopathological examination

The change in red plaques, hemorrhagic spots/plaques, erosion and bile reflux at endoscopy and the grade of active chronic inflammation and chronic inflammation in the gastric mucosa, depending on the histopathological examination of biopsy specimens, will be compared between visits one and six, according to the consensus on CG in China.

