#### The change in the patient-reported outcome instrument for chronic gastrointestinal diseases

Although the symptoms of chronic gastritis are not specific, the relief of clinical symptoms remains a major therapeutic aim. The patient-reported outcome (PRO) instrument for chronic gastrointestinal diseases (http://www.proqolid.org/) [20], a 6-dimension, 35-item instrument, will be performed on visits one and six, and the results will be used to compare the two visits to assess any changes in quality of life. The 35 items of the instrument are the following: fatigue, disturbed sleep, no hunger sensation, decreased appetite, afraid of society, dry mouth or bitter taste in mouth, bad breath, pharyngeal foreign body sensation, acid regurgitation, hiccup or belching, nausea or vomiting, burning pain behind the sternum, retrosternal pain, stomachache, gastric distension, gastric discomfort, stomach burning, abdominal pain, abdominal distension, degree of retrosternal pain, degree of heartburn, degree of stomachache, degree of gastric distension, degree of abdominal pain, degree of abdominal distension, diarrhea, constipation, incomplete sensation after defecation, defecation urgency, weight loss, emotional fluctuation, anxiety or nervous, worry about disease, impact on social activities and impact on family status and function. All of the items fall into five levels, which are scored as 0, 1, 2, 3 or 4, except for decreased appetite, which is grouped into four levels and scored as 0, 1, 2 or 3. The final score will be determined by the sum of all symptom scores.

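### LOCF carries the baseline forward, as a change of exactly zero, for endoscopy, histology and PRO in patients without a visit-six assessment

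*Protocol article*

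**What the plan says.** The Statistical analysis section of the protocol article sets the population: "A full analysis set (FAS) is the primary analysis population for efficacy with an intention-to-treat principle". It names one missing-data method: "We estimate the missing data using the last observation carried forward (LOCF) method". The stated purpose is to keep in the final analysis everyone who entered the trial. No outcome is excepted. The section then says that therapeutic effect is evaluated at visit six under the PPS, or at the time of withdrawal under the FAS.

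Three places give the timing of the outcomes at issue:

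- Endoscopic and histopathological examination (secondary outcomes): the findings "will be compared between visits one and six, according to the consensus on CG in China".
- Footnote to Table 2, on keeping the biopsy regions consistent: "For the specimens taken at the first and sixth visits".
- The PRO section: "a 6-dimension, 35-item instrument, will be performed on visits one and six".

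The VAS for epigastric pain, on which the primary outcome rests, is measured at every visit. The article describes no endoscopy, biopsy or PRO at withdrawal. The schedule figure (Figure 2) is not in the text at hand.

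**The concern.** LOCF needs a post-baseline value to carry. The VAS supplies one for a patient who attended any visit after baseline. For endoscopy, histology and the PRO, the described schedule has nothing between visit one and visit six, so the last observation of a patient who leaves early is the baseline. The rule then becomes baseline carried forward, and the patient enters the FAS as exactly unchanged.

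Zero change is neutral only if patients would not otherwise have changed. The inclusion criteria require moderate or severe chronic and/or active inflammation, so the histology scale on which a patient qualified starts at grade 2 or 3. Some improvement on that scale through regression to the mean is plausible in every arm, placebo included. If all arms improve, the arm that loses more patients looks worse for that reason alone.

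At stake is how far the FAS results for mucosal inflammation and the PRO can be trusted in a trial meant to inform phase III.

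**Working it through.** **Inputs from the protocol article.** 240 patients in three equal groups, hence 80 per arm; 20% dropout allowed for (Sample size calculation); two-sided 0.05 level (Statistical analysis). The article gives no expected change or SD for these outcomes, and no dropout by arm.

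**The plan's own figure.** The article states 66 per group for 55% v 30% with power 0.85. The unpooled two-sided formula reproduces it: (1.960 + 1.036)² × (0.55 × 0.45 + 0.30 × 0.70) / 0.25² = 8.98 × 0.4575 / 0.0625 = 65.7, rounded up to 66. This point does not dispute that figure; it takes only the 80 per arm and the 20% from that section.

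**Patients affected.** 20% of 80 is 16 per arm, or 48 of 240.

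**Formula.** Let μT and μC be the completers' mean improvements, and dT and dC the fractions without a visit-six assessment. LOCF sets those patients to 0, so the expected FAS contrast is

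(1 − dT)·μT − (1 − dC)·μC.

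**Equal dropout.** With dT = dC = 0.20 the contrast is 0.80 × (μT − μC). A completer difference of 0.50 grade is estimated as 0.40. If μT = μC the contrast is 0, and the type I error stays at 5%.

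**Unequal dropout, no drug effect.** With μT = μC = μ the contrast is (dC − dT)·μ. The variance of the change in an arm is (1 − d)(SD² + μ²) − [(1 − d)μ]². Assumed: SD 0.8, 80 per arm, and a z test at 1.96.

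Worked case, μ = 0.7 and dropout 10% v 30%:
- False difference: 0.20 × 0.7 = 0.14 grade.
- Variances: 0.9 × 1.13 − 0.63² = 0.620 and 0.7 × 1.13 − 0.49² = 0.551.
- Standard error: √[(0.620 + 0.551)/80] = 0.121.
- 0.14 / 0.121 = 1.157, which gives 21% rejections by this approximation and about 22% in 20,000 simulated trials.

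| Improvement in both arms (assumed) | Dropout (assumed) | False difference | False-positive rate |
|---|---|---|---|
| any | 20% v 20% | 0 | 5% |
| 0 | 10% v 30% | 0 | about 5% |
| 0.3 | 15% v 25% | 0.03 | about 6% |
| 0.3 | 10% v 30% | 0.06 | about 8 to 9% |
| 0.7 | 15% v 25% | 0.07 | about 9% |
| 0.7 | 10% v 30% | 0.14 | about 22% |
| 1.0 | 10% v 30% | 0.20 | about 34% |

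Swapping the dropout rates between the arms reverses the sign and leaves the size unchanged. With integer grade changes (0, −1, −2) in place of normal scores, a 10% v 30% setting gave 0.14 grade and 25%, so the result does not hang on the normal model.

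**The case against.** **Scope and certainty.** The schedule figure is not shown, and evaluating the FAS at the time of withdrawal suggests that some assessment takes place then. That stands as a limit: the article describes no endoscopy, biopsy or PRO at withdrawal, but their absence from the full schedule cannot be proved. An examination actually done at withdrawal would be carried forward instead.

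**Generic wording.** The analysis text also evaluates changes at visits two to five without exception, so it seems written for serially measured scores, and handling by outcome could sit in an SAP. But the article states the rule and the sampling times, and together they give zero change. This is a stated rule that misfires, not an omitted detail.

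**Secondary outcomes, with a check.** True. The PPS avoids this imputation and would help to expose a result driven by it. It is ranked second, however, and also excludes non-adherent patients.

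**Stronger readings a reader might infer.** One is that LOCF will manufacture a mucosal benefit. The document does not support that: its only dropout figure is 20% overall, inflation needs clearly unequal dropout together with improvement in all arms, and the bias runs against the drug if the active arms lose more patients. Another is that regression to the mean affects all these outcomes. The entry criterion sets no minimum for endoscopic grades or the PRO, and its and/or wording leaves one histology scale free, so the argument reaches only the scale that qualified the patient. A third is that the primary outcome shares the defect. It does not, because the VAS is measured at every visit.

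**Conclusion.** The point holds in this limited form. As the article describes the visits, LOCF enters a change of exactly zero for endoscopy, histology and PRO in every FAS patient without a visit-six assessment; at the planned 20% dropout that is about 16 of 80 per arm. With equal dropout the cost is dilution to 80% of the completer difference, without type I error inflation. With unequal dropout and improvement in all arms there is bias in either direction. For 10% v 30% it ranges from 0.06 grade (about 8 to 9% false positives) to 0.14 grade (about 22%) as the common improvement goes from 0.3 to 0.7 grade. Those figures rest on assumed improvement, SD and dropout by arm, and they illustrate rather than predict. The point concerns secondary outcomes and leaves the primary analysis untouched. It is worth correcting because the remedy is cheap and recruitment had not begun when the article was submitted.

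**What to change.** - Exempt outcomes assessed only at visits one and six from LOCF.
- Analyse the observed visit-six values, adjusted for the visit-one value and centre, with multiple imputation by arm for the missing ones.
- Impute endoscopy and histology from the baseline value and centre. For the PRO, add the intermediate symptom and VAS scores. The Discussion reports no obvious correlation of symptoms with histology or endoscopic grading, so those scores would add little for the mucosal outcomes.
- Keep baseline carried forward only as a sensitivity analysis.
- Collect the PRO at the withdrawal contact. No extra endoscopy is asked for.

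The cost is a change of analysis wording, one imputation run and a few minutes of questionnaire time per withdrawing patient. The downside is fewer observed values and slightly wider intervals for endoscopy and histology, and reliance on a missing-at-random assumption, which the sensitivity analysis helps to probe.
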